### Study design and setting

We will conduct a prospective multi-centered three-arm, single-blind, superiority RCT. The study will recruit participants from three settings: (1) the ED of the Schwartz/Reisman Emergency Medicine Center, (2) the Granovsky-Gluskin Family Medical Centre at Mount Sinai Hospital, and (3) the ED of the North York General Hospital. All three sites are in Toronto, Ontario, Canada. Mount Sinai Hospital is an urban tertiary care center with an annual census of 65,000 ED patients. North York General is a university-affiliated academic community hospital with an annual census of 118,000 ED patients. For both hospitals, 17–20% of ED patients were 70 years and older over the last 3 years.

### Hypotheses

Our primary hypothesis is that participants who receive the intergenerational HOW R U? intervention will have superior outcomes compared to the waitlist control group and to the same-generation peer support HOW R U? intervention. Our second hypothesis is that participants with higher perceptions of generativity will have greater reductions in SIL. Third, we hypothesize that participants in the intergenerational intervention will have higher perceptions of generativity after 12 weeks than the same-generation peer support and waitlist control groups.

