**Discussion:**

We hypothesize participants receiving the intergenerational intervention will show improved outcomes compared to the control group and peer support HOW R U? intervention. We also hypothesize that participants with higher perceptions of generativity will have greater reductions in SIL than their lower generativity counterparts. Aging is experienced diversely, and social interventions combatting associated SIL should reflect that diversity. As part of a program of research following the Obesity-Related Behavioral Intervention Trials (ORBIT) model, the findings of this RCT will be used to define which intervention characteristics are most effective in reducing SIL.

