### Study purpose

Our primary outcomes are to assess whether the intergenerational HOW R U? intervention (1) reduces SIL more than the waitlist control group at study week 12 and (2) reduces SIL more than the current same-generation peer support HOW R U? intervention at study week 12.

Secondary outcomes include assessing:The impact of the intergenerational HOW R U? intervention on (i) SIL at study week 24, (ii) depression, (iii) quality of life, (iv) functional status, (v) generativity, (vi) participant’s perceived self-benefit, and (vii) participant’s perceived benefit for the volunteer delivering the HOW R U? intervention at study weeks 12 and 24.Participant stated preferences for intergenerational versus same-generation peer support HOW R U? intervention prior to randomization. Note, participants will be randomized regardless of their intervention preference.

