Key inclusion and exclusion criteria	Inclusion Criteria 1. Community-dwelling person 70 years of age and older receiving care from the ED, Family Medicine or Geriatric clinics at the two participating sites (MSH, NYGH) 2. Baseline de Jong loneliness score of 2.0 will be required for participating in the trial Exclusion Criteria 1. Age less than 70 years of age 2. Patients with communication problems (critically ill, unconscious, language barrier, speech impairment or otherwise unable to provide consent) or admission to a hospital for greater than 72 h) 3. Patients with severe cognitive impairment or those with living in nursing homes who are dependent on others for their activities of daily living 4. Patients without any mobile phone or landline Volunteer Inclusion Criteria 1. Peer-support volunteers will be 60 years of age or older 2. Intergenerational volunteers will be between 19–39 years of age
Study type	Interventional Allocation: Randomized interventional model. Parallel assignment. Outcome assessor masking Primary purpose: Supportive Care
Date of first enrolment	November 1, 2021
Target sample size	141
Recruitment status	Recruiting
Primary outcome(s)	1. Change in loneliness using De Jong Gierveld 6-item Loneliness Scale from baseline to 12 weeks
Key secondary outcomes	1. Change in loneliness using De Jong Gierveld 6-item Loneliness Scale from baseline to 24 weeks 2. Change in perceived social support using Lubben Social Network Scale from baseline to 12 and 24 weeks 3. Change in mood using Geriatric Depression Scale from baseline to 12 and 24 weeks 4. Change in baseline cognition using “Brief Alzheimer’s Screening Test” from baseline to 12 and 24 weeks 5. Change in Quality of Life using Euro-Qual 5 Dimensions 5 Levels from baseline to 12 and 24 weeks 6. Change in Functional Status using Older Americans Resource Scale from baseline to 12 and 24 weeks 7. Change in self-perceptions of generativity using Loyola Generativity Scale from baseline to 12 and 24 weeks 8. Perceived benefit to participant at 12 and 24 weeks 9. Perceived benefit to volunteer at 12 and 24 weeks

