### Outcome measures

The primary outcome is loneliness as measured using the six-item De Jong loneliness scale after completion of the intervention (weeks 12–14 of the study). The De Jong scale has been extensively validated in older populations and is divided into four clinically relevant categories: 6—severe loneliness, 4–5—moderate-to-severe loneliness, 2–3—low loneliness, and 0–1—no loneliness [12].

The secondary outcomes are the following: (1) the de Jong loneliness Scale at 12 weeks post-completion of the intervention to assess sustainability (study week 24); (2) six-item Lubben’s Social Network Scale [18]; (3) five-item Geriatric Depression Scale to assess mood [19]; (4) Brief Alzheimer’s Screening Test to assess baseline cognitive performance [20]; (5) EQ-5D-5L to assess perceived health-related quality of life in the areas of self-care, mobility, usual activities, pain/discomfort, and anxiety/depression [21]; (6) the Older Americans Resource Scale to assess functional status [22]; (7) the Loyola Generativity Scale to assess generativity [23]; (8) perceived benefit by the participant; and (9) benefit to the volunteer as perceived by the participant. The standardized measurement instruments selected for the trial have been extensively validated in older adults. The Loyola Generativity Scale has demonstrated good interrater reliability as well as responsiveness in trials of older adults [24, 25]. To assess the secondary outcome of participant preference for same-generation peer support versus intergenerational HOW R U? intervention, we will use a 5-point Likert scale with the following options: “I strongly prefer peer support,” “I prefer peer support,” “neutral,” “I prefer intergenerational,” and “I strongly prefer intergenerational”. Please see Appendix 3 for full details.

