### Analysis

All analyses will use SAS Version 9.4 (SAS Institute, Cary, NC, USA). A two-sample two-sided test of proportions will be used to assess the primary outcome of loneliness in the control group versus the intergenerational HOW R U?, and the control group versus the same-generation peer support HOW R U? intervention. Improvements in the binary outcome of the loneliness category of the De Jong Loneliness Scale will be assessed using a logistic regression model, and results will be reported as odds ratios with the corresponding 95% confidence intervals. The variance inflation factor (VIF) will be calculated to assess for multicollinearity before the logistic regression model is built such that if two variables are highly correlated (i.e., VIF > 4 or tolerance < 0.25), only one of the two variables is retained for the final model. To compare the secondary outcomes, they will be reported as means with corresponding 95% confidence intervals.

Potential missing data will be managed as follows. For logistic regression, participants with more than 15% missing data for confounding variables will be excluded from the analysis. Note that in the main trial, less than 5% of participants would have been excluded. For participants with less than 15% missing data, we will use imputation for confounding variables. Participants with missing outcome data will be excluded from analysis (i.e., lost to follow-up). Note that after two-thirds of the participants have been enrolled, we will assess the loss-to-follow-up rate and adjust the enrollment accordingly. For example, if the lost-to-follow-up rate is 20%, we will increase the enrolment by 20%. To manage protocol nonadherence, participants will be analyzed using intention-to-treat analysis regardless of their adherence to the protocol.

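### The secondary outcomes are to be compared by reporting means with 95% intervals, which does not give the between-arm differences that the aims and the generativity hypothesis need

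*Protocol article*

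**What the plan says.** The Analysis section gives one sentence on how the secondary outcomes are compared: "To compare the secondary outcomes, they will be reported as means with corresponding 95% confidence intervals". It does not say whether the means are of follow-up scores or of changes, or whether the intervals belong to each arm or to a difference between arms.

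The claims that these outcomes serve are comparative. The third statement under Hypotheses is that "participants in the intergenerational intervention will have higher perceptions of generativity after 12 weeks than the same-generation peer support and waitlist control groups". Study purpose lists as secondary aims the effect of the intergenerational intervention on later loneliness and isolation, depression, quality of life, function and generativity. Table 2 registers most of these as changes, for example: "Change in self-perceptions of generativity using Loyola Generativity Scale from baseline to 12 and 24 weeks".

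The primary hypothesis is broad: "participants who receive the intergenerational HOW R U? intervention will have superior outcomes compared to the waitlist control group and to the same-generation peer support" arm. The Discussion paragraph of the abstract is equally broad: "We hypothesize participants receiving the intergenerational intervention will show improved outcomes compared to the control group and peer support HOW R U? intervention". Neither names an outcome or a time point. Outcome measures does: "The primary outcome is loneliness as measured using the six-item De Jong loneliness scale after completion of the intervention (weeks 12–14 of the study").

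**The concern.** A mean with its own interval describes one arm. The effect of the intervention is a contrast, and its uncertainty is that of the difference. Two arm-specific intervals do not show that uncertainty directly, and the usual shortcut, looking for overlap, is a much stricter rule than a 5% test. Real effects on generativity, mood or quality of life could be read as absent because two intervals touch. This matters most for generativity, the mechanism that the trial sets out to study and the subject of a directional hypothesis with two comparators.

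The broad wording of the primary hypothesis is a lesser matter. Taken alone, it does not tell the reader which result decides it.

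**Working it through.** **Plan's own figure.** The article gives no power or precision figure for any secondary outcome, so there is none to reproduce. Its 47 per arm and power above 80% concern the proportion improving by one loneliness category. The 80% below is only a reference level.

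**Inputs.** 95% intervals (Analysis). Equal arms of 47 (Sample size and power; 3 × 47 = 141, the target in Table 2). Assumed: approximately normal means, independent arms and the same standard error *s* in each arm.

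**Step 1: interval on the difference.** The standard error of the difference is √(s² + s²) = s√2. The interval excludes zero when |difference| > 1.96 × s√2, that is, |z| > 1.96. Two-sided size is 5%.

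**Step 2: non-overlap of two arm-specific intervals.** The intervals separate when |difference| > 1.96s + 1.96s = 3.92s. Dividing by s√2 gives |z| > 3.92/√2 = 2.77.

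**Step 3: size under the overlap rule.** 2 × [1 − Φ(2.77)] = 0.0056, about 0.6% per comparison.

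**Step 4: power under the overlap rule.** A comparison with 80% power at the two-sided 5% level has an expected z of 1.96 + 0.84 = 2.80. Under the overlap rule its power is 1 − Φ(2.77 − 2.80) = Φ(0.03) ≈ 0.51. True differences with an observed |z| between 1.96 and 2.77 are missed.

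**Step 5: unequal standard errors.** In general the threshold is 1.96 × (s₁ + s₂)/√(s₁² + s₂²). If one standard error is twice the other, this is 1.96 × 3/√5 = 2.63. The size is then about 0.9% and the power Φ(2.80 − 2.63) ≈ 0.57. The loss shrinks but does not go away.

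**Step 6: is the baseline value available?** Table 1 marks the De Jong, Lubben, depression, cognition, EQ-5D-5L, functional status and generativity scales before the intervention and at both follow-ups. Data collection also says that baseline assessments are taken. With baseline-to-follow-up correlation ρ, the variance of the estimated difference, relative to comparing follow-up scores alone, is 1 − ρ² after baseline adjustment and 2(1 − ρ) for change scores. The article gives no ρ. Over an assumed range of 0.6 to 0.8:

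| ρ | Baseline-adjusted, 1 − ρ² | Change score, 2(1 − ρ) |
|---|---|---|
| 0.6 | 0.64 | 0.80 |
| 0.8 | 0.36 | 0.40 |

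Adjustment is at least as precise as either alternative and also settles whether the means are of scores or of changes.

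**The case against.** The strongest reply is that the sentence is shorthand. It opens by speaking of comparison, the authors may well intend intervals on differences, and nothing in the article prescribes an overlap rule. An analysis plan, not shown here, may spell out the contrasts. This stands in part: the overlap figures apply only if the arm intervals are read that way. But the sentence is a stated method, not an omission, and what it names is not a contrast.

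A reader might go further and infer that the broad primary hypothesis, together with nine secondary outcomes labelled key, lets any chance secondary result supply a superiority claim. The documents do not support that reading:

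- Study purpose limits the primary aims to whether the intervention "reduces SIL more than the waitlist control group at study week 12" and "reduces SIL more than the current same-generation peer support HOW R U? intervention at study week 12".
- Table 2 and Outcome measures name De Jong loneliness as the one primary outcome, and the sample size is built on its categories. A primary and secondary order therefore exists.
- Hypotheses ranks generativity as a separate third hypothesis, which would be redundant if the first already covered every outcome.
- The label key is a row heading in a registration data-set table. The body text simply says secondary.
- No passage lets a secondary outcome establish superiority, and the primary hypothesis requires superiority to both comparators.
- Ordering of secondaries and exploratory labels are commonly left to an analysis plan.

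What remains is a wording gap. Study purpose speaks of social isolation and loneliness together, so the specific scale comes only from Table 2 and Outcome measures. The hypothesis should carry it.

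**Conclusion.** The point holds in a limited form. The stated method for secondary outcomes does not produce the between-arm differences that the secondary aims and the generativity hypothesis call for. If arm-specific intervals are judged by overlap, the size per comparison is about 0.6% and power of 80% falls to about 51%. These figures assume equal standard errors, independent arms and approximate normality. The loss is smaller, with power about 57%, when one standard error is twice the other. If the intervals are meant for differences, the loss does not arise and only the wording needs to say so.

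The point does not affect the primary analysis or the sample size. It supports no claim of inflated error across the secondary outcomes and no demand for a gated test of generativity.

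**What to change.** In Analysis, replace the sentence on secondary outcomes. For each continuous secondary outcome measured at baseline, report the between-arm difference in mean at weeks 12 and 24, adjusted for the baseline value of that outcome, with a 95% confidence interval. Give two contrasts: intergenerational minus waitlist, and intergenerational minus peer support. Arm means can still be shown as description.

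As a minor alignment, word the primary hypothesis, under Hypotheses and in the abstract, as De Jong loneliness at weeks 12–14 against each comparator, so that secondary results are read as supportive.

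The cost is a few sentences of text and a standard regression model in the software already named. No additional data, visits or participants are needed.

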### Recruitment and training

Participants will be recruited from the EDs of Mount Sinai Hospital and North York General Hospital as well as the Granovsky-Gluskin Family Medical Centre at Mount Sinai Hospital. Same-generation peer support volunteers will be vetted and approved by the existing hospital volunteer programs at Mount Sinai Hospital and North York General Hospitals. We will also use a social media recruitment campaign if required. Volunteers for the intergenerational intervention group will be recruited via university student groups associated with the University of Toronto and Western University. Volunteers of both the same-generation peer support and intergenerational HOW R U? interventions will attend a standardized, interactive 3-h training session. Content discussed will include ageism, mental health and aging, empathetic listening, validation, available community supports, confidentiality, and safety protocols. HOW R U? uses a strength-based approach focusing on empowerment and the participant’s strengths as previously developed by Lowthian et al. [4].

### Inclusion and exclusion criteria

Participant inclusion criteria are as follows: (1) age 70 years and older and (2) a minimum baseline six-item De Jong loneliness score of 2/6, corresponding to loneliness or high risk of loneliness [13]. We will accept referrals from participating ED and clinics as well as self-referrals from participants to improve recruitment.

We will exclude individuals (1) living in nursing homes; (2) with significant cognitive impairment as assessed by the Adamis capacity assessment [14, 15]; (3) with difficulty communicating (i.e., critically ill, unconscious, unable to communicate in English, speech impairment or otherwise unable to provide consent); (4) without access to a telephone; and (5) admitted to hospital for > 72 h. Volunteers will be excluded if they are less than 19 years of age and, in the case of intergenerational volunteers, if they are over 39 years of age. Same-generation peer support volunteers less than 60 years of age will be excluded.

### Randomization and blinding

We will use a computerized number generator to randomize to the three study arms in blocks of three, stratified by referral source. This will be an open-label trial. We will use an outcome assessment blinding process developed in our previous trial: outcomes assessors are blinded to the intervention group and record the primary outcomes at the start of follow-up calls to prevent accidental unblinding. Participants are also instructed not to reveal which intervention to any research staff, and any instances of unblinding will be documented by the outcome assessor. No formal auditing process is implemented for this trial.

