### Intervention

Following randomization, research assistants will attempt to match volunteers and participants based on (1) any gender preferences and (2) shared interests or hobbies. This matching process will serve to promote adherence to intervention protocols as will the standardized 3-h volunteer training session which will teach strategies for volunteers to encourage participant engagement. Finally, we have attempted to minimize the research burden on participants to further limit potential contributors to nonadherence. For example, there is no interim data collection between enrollment and completion of the study. We are monitoring adherence by logging the time and duration of phone calls between volunteers and participants. Note, as the study’s intervention is a social interaction and not a pharmaceutical trial, drug tablet returns and laboratory tests are not applicable.

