### Data collection

Research assistants will collect data for all groups over the telephone. Initial screening of potential participants by research staff involves the six-item De Jong loneliness scale which is described in further detail below. We will then collect demographic data including age, gender, living arrangement, pet ownership, educational attainment, technology profile index (modified), and baseline assessments of primary and secondary outcomes (see the “Outcome measures” section) from eligible participants who provide informed consent. Trained research staff will obtain verbal informed consent for this study as approved by all participating institutional REBs (see Appendix 2 for the informed consent model). Research staff are not involved in the clinical management of participants to avoid the perception of coercion. In order to allocate patients to specific arms, a statistician independent of the trial management will use a computer procedure to generate a variable block randomization list with blocks varying between four and eight. Note, as in our previous trial, research staff involved in outcome assessment will be blinded to randomization status. After completion of the 12-week intervention, research assistants will reassess outcomes within 2 weeks (study week 12–14) and 12 weeks (study week 24). To minimize the potential Hawthorne Effect, study endpoints will be collected only upon completion of the intervention [17]. Personal health information is removed from all study databases. Deidentified data will be stored in a password-protected computer accessible only by the study’s research assistants and corresponding author and will remain confidential. As this is a minimal-risk study, no formal data monitoring committee was required by our REB. A study committee consisting of the principal investigator, coauthors, and statistician will have regular meetings once a quarter to discuss ongoing data collection, quality, and outcomes. Note, no interim analyses are planned in this minimal-risk study.

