### Sample size and power

Each group will consist of a sample of 47 subjects which will detect a 13.9–28.1% difference between the treatment and control groups in the proportion of people who improve by one category (e.g., from severe loneliness to moderate-to-severe loneliness) with a power greater than 80%. This assumes that up to 15% of control group participants may have a spontaneous improvement in loneliness categories. With these sample sizes, three comparisons may be made: intergenerational intervention to the control group, same-generation peer support intervention to the control group, and intergenerational to the same-generation peer support intervention.

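### The protocol states two incompatible block schemes for the same three-arm allocation; the variable one does not suit 1:1:1, and the fixed one is the most predictable permuted-block scheme

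*Protocol article*

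**What the plan says.** The Protocol article, Study design and setting, describes the design: "We will conduct a prospective multi-centered three-arm, single-blind, superiority RCT". Sample size and power plans equal arms: "Each group will consist of a sample of 47 subjects". With three arms this gives the target of 141 in the registration table.

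The allocation rule appears in two places:

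- **Randomization and blinding:** a computerised generator will "randomize to the three study arms in blocks of three, stratified by referral source". The same section adds "This will be an open-label trial" and limits blinding to the outcome assessors.
- **Data collection:** "a statistician independent of the trial management will use a computer procedure to generate a variable block randomization list", with sizes running from four to eight. Strata are not mentioned there.

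Two other statements bear on who may see allocations. The Intervention section says "Following randomization, research assistants will attempt to match volunteers and participants", so some research assistants know the assigned arm. Data collection says "Trained research staff will obtain verbal informed consent for this study".

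**The concern.** Both sentences are current text about the same randomisation. A reader cannot tell which block scheme was used, and each has a weakness of its own. Most of the variable sizes cannot be divided equally among three arms. A fixed block of three is the smallest that can hold three arms, and so gives away the most about the next assignment.

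Foreknowledge of the next assignment matters here. Participants state before randomisation whether they prefer the peer or the intergenerational version, and the Discussion names a mismatch between preference and assignment as a possible confounder of the primary outcome. If someone enrolling participants could foresee the next arm, the timing of enrolment could be adjusted to it. Blinded outcome assessment would not correct this, because the bias would enter before assessment.

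**Working it through.** **Inputs.** Three arms (Study design and setting). Equal arms of 47 (Sample size and power); 3 × 47 = 141, which agrees with the registration table. Block size 3, stratified (Randomization and blinding). Block sizes 4 to 8 (Data collection).

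**Step 1: compatibility.** Three is not in the range 4 to 8, and one rule is fixed while the other varies. No reading of the text satisfies both.

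**Step 2: does the variable scheme fit 1:1:1?** A block holds equal numbers of three arms only if its size is a multiple of three.

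| Block size | Multiple of 3? | Closest split |
|---|---|---|
| 4 | no | 2/1/1 |
| 5 | no | 2/2/1 |
| 6 | yes | 2/2/2 |
| 7 | no | 3/2/2 |
| 8 | no | 3/3/2 |

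Four of the five sizes fail. If only even sizes are meant (4, 6, 8), two of three fail. If only 4 and 8 are meant, both fail.

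**Step 3: predictability of fixed blocks of three.** Suppose the guesser knows the block size and all earlier assignments in the stratum, and always names an arm with the most places left. The chance of being right is 1/3 for the first place in the block, 1/2 for the second and 1 for the third:

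(1/3 + 1/2 + 1) / 3 = (11/6) / 3 = 61.1%, against 33.3% by chance.

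One allocation in three is certain. If all blocks are complete, that is 141 / 3 = 47 participants.

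**Step 4: comparison with larger multiples of three, sizes known to the guesser.** The same guessing rule, enumerated exactly, gives an expected 101/30 correct guesses in a block of 6 and 4021/840 in a block of 9. An allocation is certain once only one arm has places left, so the number of certain allocations is the expected length of the final run of one arm:

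- block of 6: 1 + 1/5 = 1.2, and 1.2 / 6 = 20%
- block of 9: 1 + 2/8 + (2/8)(1/7) = 1.286, and 1.286 / 9 = 14%

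| Block size (known) | Correct guesses | Certain allocations |
|---|---|---|
| 3 | 61.1% | 33.3% |
| 6 | 56.1% | 20.0% |
| 9 | 53.2% | 14.3% |

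These are figures for known sizes. The gain from varying the size and withholding it was not computed.

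**Step 5: how much of the list may remain.** By the Trial status section, recruitment began on 1 November 2021, this version is dated 3 October 2023, and completion was expected about 1 February 2024. That is about 23 of 27 months. If enrolment were even over time (an assumption), about 141 × 23/27 = 120 participants would already have been allocated, leaving about 21.

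**The case against.** The contradiction over block size is not in dispute; the case on the other side concerns its consequences.

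- **Foreknowledge.** A reader might infer that, because the trial is open-label, recruiters could foresee every third assignment. The documents do not support that. They say that research assistants match volunteers after randomisation and that research staff obtain consent, but not that the same people do both. Participants are told not to disclose their arm to research staff. How allocations are held and released is detail that an article commonly leaves to the full protocol. This objection stands: predictability applies within a referral-source stratum, to someone who knows its earlier assignments. Generation of the list by an independent statistician protects the list, but does not make a block of three less predictable.
- **Strata.** A reader might take the silence on strata in Data collection as a second contradiction. It is not one. That section does not deny the stratification stated elsewhere; only the block sizes conflict.
- **Equal arms.** A reader might argue that blocks of 4, 5, 7 or 8 put the 47/47/47 split at risk. The argument proves too much, since 141 is not a multiple of 6 or 9 either, and sound schemes would also not guarantee an exact split. The point about divisibility is that the stated sizes do not suit the design, not that a material imbalance has been shown.
- **Size of the gain.** Against known blocks of 6 or 9, the fall in correct guesses is from 61% to 56% or 53%, which is modest. This also stands.

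**Conclusion.** The point holds as an unreconciled contradiction in the allocation method. It is wrong as written and cheap to correct. The variable scheme does not suit 1:1:1 allocation, since only one of its five possible sizes is a multiple of three. The fixed scheme is the most predictable permuted-block scheme for three arms: 33% of allocations certain and 61% guessed correctly, for someone who knows the block size and the earlier assignments in the stratum. The block size is public; access to the earlier assignments by enrolling staff is plausible but not stated. Selection bias is therefore a conditional risk, and the documents do not show that it occurred or that staff were placed to cause it. The planned sample size is not affected.

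**What to change.** State in both Randomization and blinding and Data collection the one scheme actually used, including its strata, and delete the other. If fixed blocks of three were used, report this as a limitation on allocation concealment.

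For any allocations not yet made, have the independent statistician generate a 1:1:1 list, stratified by referral source, with randomly varying block sizes that are multiples of three. Keep the sizes out of the public text and from recruiting staff until enrolment ends; printing them would defeat the purpose.

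The cost is two corrected sentences and, if any allocations remain, a short new list. The downside is a slightly larger possible imbalance within strata than with blocks of three. With recruitment close to its planned end, the new list may affect few participants, so the statement of what was done is the main correction.
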